## Abstract

**Background:**

A chronic condition, drug addiction, requires long-term multipronged health care and treatment services. Community-based approaches can offer the advantages of managing integrated care along the care continuum and improving clinical outcomes. However, scant rigorous research focuses on sustainable, community-based care and service delivery.

**Objective:**

This protocol describes a study aiming to develop and test an intervention that features the alliance of community health workers and family members to provide integrated support and individualized services and treatment for people who use drugs (PWUD) in community settings.

**Methods:**

Based on the National Institute on Drug Abuse’s Seek-Test-Treat-Retain (STTR) framework, an intervention that provides training to community health workers will be developed and piloted before an intervention trial. Trained community health workers will conduct home visits and provide support for PWUD and their families. The intervention trial will be conducted in 3 regions in Vietnam, with 60 communities (named communes). These communes will be randomized to either an intervention or control condition. Intervention outcomes will be evaluated at baseline and at 3, 6, 9, and 12 months. The primary outcome measure is PWUD’s STTR fulfillment, consisting of multiple individual fulfillment indicators across 5 domains: Seek, Test, Treat, Retain, and Health. The secondary outcomes of interest are the community health workers’ service provision and family members’ support. The primary analysis will follow an intention-to-treat approach. Generalized mixed-effects regression models will be used to compare changes in the outcome measures from baseline between intervention and control conditions.

**Results:**

During the first year of the project, we conducted formative studies, including in-depth interviews and focus groups, to identify service barriers and intervention strategies. The intervention and assessment pilots are scheduled in 2023 before commencing the trial. Reports based on the baseline data will be distributed in early 2024. The intervention outcome results will be available within 6 months of the final data collection date, that is, the main study findings are expected to be available in early 2026.

**Conclusions:**

This study will inform the establishment of community health workers and family members alliance, a locally available infrastructure, to support addiction services and care for PWUD. The methodology, findings, and lessons learned are expected to shed light on the addiction service continuum’s implementation and demonstrate a community-based addiction service delivery model that can be transferable to other countries.

**Trial Registration:**

ClinicalTrials.gov NCT05315492; https://clinicaltrials.gov/ct2/show/NCT05315492

**International Registered Report Identifier (IRRID):**

DERR1-10.2196/44219

## Introduction

Drug addiction, such as opioid use disorder, is one of the most significant public health issues globally [1]. Medication-assisted therapies (MAT), including methadone and buprenorphine or naloxone, are in place to prevent opioid-related overdose and the spread of infectious diseases [2-5]. However, substantial barriers exist to the provision and use of MAT because of the shortage of addiction specialists to prescribe and monitor MAT, especially in remote areas [6,7]. For example, community MAT programs require community members’ support and resources to train community health care workers [6,7].

Mobilization of community-based systems in the service delivery model has been advocated as a desirable strategy to reduce the current gap in MAT [8-12]. In addition, drug addiction, as a chronic condition, requires long-term multipronged health care [13,14]. Community-based approaches can offer the advantages of managing integrated care along the care continuum and improving clinical outcomes [15-18]. However, there is a lack of research focusing on the systematic implementation of MAT and its related service delivery in community care settings [18].

Commune Health Centers (CHCs) are grassroots health care facilities in rural Vietnam, where essential preventive care, initial diagnosis, and referral services can be accessed by residents [19]. Vietnam is one of the first countries to decentralize MAT delivery from centralized treatment sites to community settings [20,21]. However, its CHC-based MAT programs face challenges, such as community health workers (CHWs) lack of capacity in treatment services, misconceptions of harm reduction, and stigmatizing attitudes toward PWUD [22]. Hence, adherence to MAT has been suboptimal, and the patient dropout rates are alarmingly high [23,24].

In Vietnam, the family presents a critical source of support for people who use drugs (PWUD) [25-27]. Families are commonly the source of daily care and financial, emotional, tangible, and informational support for opioid users’ care seeking. The support given by family members can significantly impact the health care use and outcomes of PWUD [28,29]. At the same time, close family members of PWUD often struggle with mental health issues, impaired social adjustment, poor work relations, decreased social participation, and increased intrafamily dysfunction [30,31]. These challenges have jeopardized the family’s capacity to support PWUD in care seeking and adherence.

Current health care infrastructure and culture in Vietnam provide an opportunity to test a community-based service delivery model for addiction care and treatment. We plan to develop and test an intervention that features the alliance of community health workers and family members to provide integrated support and individualized treatment services for PWUD in community settings.

## Methods

### Theoretical Framework

The National Institute on Drug Abuse’s Seek-Test-Treat-Retain (STTR) initiative provides a framework to guide the delivery of addiction services [32,33]. This approach requires reaching out to PWUD and understanding their health needs (Seek), engaging them in routine physical examinations and laboratory testing (Test), initiating MAT and treatment of comorbidities (Treat), and facilitating treatment adherence and long-term, uninterrupted care (Retain). Based on the theoretical framework, we plan to synergize the support from CHWs and family members as two of the most essential enabling factors to build a respectful, accepting, and supportive addiction care continuum for PWUD (Figure 1). Specifically, CHWs will be trained to provide individualized care with a nonstigmatizing attitude. In addition, family members will be mobilized to give continuous support to PWUD’s service seeking and adherence. The coalition between CHWs and family members will provide a locally available infrastructure to support addiction treatment services, resulting in effective and sustainable outcomes.

**Figure 1 figure1:**
[figure not shown]
Theoretical Framework.

### Intervention Development and Pilot

Formative studies, including focus groups and in-depth interviews, will inform intervention development and implementation plan. A total of 3 CHW focus groups and 3 focus groups with community representatives focus on identifying service gaps and effective local strategies to address the challenges. In-depth interviews with PWUD and family members will identify the needs in support, barriers, and facilitators to maintaining service engagement and retention. Following the formative studies, a multidisciplinary work group will be formed and go through 3 steps: (1) reviewing the problem and identifying intervention outcomes, (2) adapting evidence-based strategies to local infrastructure and culture, and (3) developing the intervention implementation and evaluation plan. A pilot version of the intervention program will be produced and followed by an intervention pilot study. The pilot will include a full implementation of intervention activities. In-depth interviews with participants and intervention team members will be conducted to refine the intervention. We will also finalize recruitment procedures and assessment batteries in this phase.

### Cluster-Randomized Controlled Trial

#### Study Design

The intervention trial aims to test the efficacy of the intervention, primarily with PWUD outcomes, and secondly, at family members and CHW levels. We hypothesize that (1) the intervention will improve PWUD’s service fulfillment along the addiction service continuum, as well as their health outcomes; (2) the intervention will enhance CHWs’ provision of addiction-related service provision for PWUD and support of their family members; and (3) the intervention will improve family members’ support for PWUD’s engagement in the addiction continuum. The trial will be conducted in 3 regions in Vietnam. These regions represent geographical variations in the country. The trial will include 60 CHCs, randomized to either an intervention or control condition. We propose to enroll 720 PWUD and 720 family members (12 families per CHC) as well as 180 CHWs (3 per CHC). Intervention outcomes will be evaluated at baseline and every 3 months after that (Figure 2). We plan to select communes with the highest number of PWUD in each region to ensure adequate participants. The selected CHC in each region will be paired based on the number of PWUD. Within each pair, the CHC will be randomized after baseline.

**Figure 2 figure2:**
[figure not shown]
Study design.

#### Eligibility and Recruitment

To recruit PWUD, we will post project recruitment flyers in major community activity sites, such as local commune culture centers, hospitals or pharmacies, and other places where local PWUD usually gather. PWUD interested in the study can contact our recruitment staff using the information printed on the flyers. Recruitment staff will meet with potential participants individually to screen for eligibility. Eligibility criteria include (1) age of 18 years and older, (2) having a history of drug use, (3) having disclosed the drug-using status to at least one of the family members and being willing to invite the family member to our study, and (4) currently residing in the selected communes. Written informed consent and consent to contacting a pointed family member will be obtained.

The consented PWUD will be asked to choose a family member in the order of closeness, usually starting from spouse, mother, father, sibling, to other relatives. The inclusion criteria for a family member are (1) age of 18 years and older, (2) being an immediate or extended family of the PWUD, and (3) knowing the PWUD’s drug-using behavior. Our recruitment staff will work with the PWUD to arrange a private meeting with the nominated family member. If the nominated family member also has a history of drug use, he or she will be enrolled as a PWUD participant, and another family member will be recruited from the family. All family member participants will sign a written informed consent.

Eligibility criteria for CHWs include age of 18 years and older and being a CHW (including doctors, assistant doctors, and nurses) who regularly provides health services to community residents. Supporting staff, including cleaners, accountants, and security personnel, will be excluded. There are usually 3 to 5 eligible CHWs in each CHC, and they will be invited to participate in the study. Written informed consent will be obtained.

#### Intervention Implementation

Based on our literature review and intervention research experience, we plan to implement an intervention that combines CHWs’ in-person group training sessions, online support groups, CHW-delivered home visits, and mobile phone text messages for PWUD and their family members. The group training sessions will be conducted with participating CHWs in the intervention arm. We anticipate conducting 2 group sessions, each lasting approximately 90 minutes. The training topics will concentrate on community-based addiction service delivery. After the initial group training sessions, online support groups will be formed to facilitate continued skill building, information sharing, networking, and problem-solving. As part of the intervention requirement, trained CHWs will work as a team to deliver individualized addiction services to PWUD and family members in the community. For each participating PWUD and their family, the trained CHW team will conduct home visits to identify PWUD’s specific needs and gaps, offer referrals, and provide social and mental health support. During the home visits, activities will be conducted with family members to release the caregiver burden, enhance family support, and address other barriers. As a supplement to the home visits, mobile phone text messages will be delivered periodically from trained CHWs to PWUD participants for health promotion and service engagement. The text messages will be adaptive to individual needs and preferences.

We will collect process evaluation data to monitor and improve intervention implementation, that is, evaluator observation, intervention activity tracking, and participant self-evaluation. For the in-person group sessions, facilitators will keep records of participants’ attendance and activities conducted in each session. The investigators and field directors will observe training sessions and use a predesigned checklist to rate the adherence to session contents, time allocation, core elements, techniques, clarity, and responsiveness. For the online group discussion, the frequency and format will be tracked. Each group member’s activity, including the initiation of threads, comments, and reactions, will be captured to determine the level of engagement. In addition, all CHWs in the intervention will be given a user-friendly service log to document their experiences and feedback on the program.

#### Data Collection

The intervention assessments will consist of self-report questionnaires and medical or service records. We will collect the information at baseline and at 3-, 6-, 9-, and 12-month follow-ups. CHWs will be surveyed using the Computer-Assisted Self-Interview method, as PWUD and family members will be assessed using the Computer-Assisted Personal Interview method. We will ask PWUD participants at each assessment to donate a urine sample to test. PWUD’s service records will be chart reviewed, and their service encounters with providers, laboratory testing dates and results, and treatment status will be collected.

#### Outcome Measures

The primary outcome measure is the PWUD’s STTR fulfillment score, which is a comprehensive score that integrates medical, behavioral, and psychosocial indicators to evaluate PWUD’s health and service engagement profile. The score consists of multiple fulfillment indicators across 5 domains: Seek, Test, Treat, Retain, and Health. Most of the indicators were suggested by the STTR Data Collection and Harmonization Initiative [14,32] and adapted to the context of Vietnam. The secondary measures of interest include CHWs’ service provision, support to PWUD and their family members, and family members’ support of PWUD’s service engagement. Other relevant indicators are listed in Figure 1. All the measures will be piloted before the trial.

#### Sample Size

The study will randomize 60 CHCs (clusters) to intervention and control conditions with a 1:1 ratio. The sample size calculation was based on the primary outcome measure. We propose enrolling 720 PWUD (360 per condition) to ensure we have 80% power at 5% significance level to detect a standardized effect size of 0.41 when comparing the mean change scores of the primary outcome between intervention and control conditions. The proposed sample size accounts for the commune-level clustering, repeated observations within PWUD, and an attrition rate up to 8% for PWUD.

#### Data Analysis

All participants will be analyzed on an intent-to-treat basis. Descriptive statistics, frequencies for demographic and baseline characteristics, and all the outcome measures will be summarized at baseline by intervention condition. For each study population, generalized linear mixed-effects regression models with appropriate link functions will be used to compare the changes in the primary outcome from baseline between intervention and control groups. Each regression model will include commune- and participant-level random effects to account for dependence within communes and repeated observations within participants. The main effects included in each model are intervention condition, visit, and a condition-by-visit interaction term. Intervention effects on the primary outcomes will be estimated using model contrasts. The preselected demographic and background characteristics (covariates) will be added to evaluate whether the intervention effects on primary outcomes remain significant. The same analytical approach will be applied to each STTR domain score and the secondary outcomes of interest. We also plan to conduct several exploratory data analyses to (1) examine the intervention effect on each STTR fulfillment indicator by subgroup, (2) explore the interrelationship among PWUD’s STTR domains or indicators to identify service gap, and (3) explore the interconnectedness of intervention effects on CHW, PWUD, and family members.

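### The primary model contrasts raw changes from baseline with separate baseline means per arm, although communes are randomised after baseline; the analysis is valid but gives up precision by an amount the article does not let one fix

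*Protocol article*

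**What the plan says.** Four statements in the protocol article matter here.

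- Study Design, on the order of events: "Within each pair, the CHC will be randomized after baseline".
- Data Analysis, on the comparison: the models will "compare the changes in the primary outcome from baseline between intervention and control groups". On the fixed effects: "The main effects included in each model are intervention condition, visit, and a condition-by-visit interaction term". On the random part: "Each regression model will include commune- and participant-level random effects to account for dependence within communes and repeated observations within participants". On the estimate: "Intervention effects on the primary outcomes will be estimated using model contrasts".
- Data Analysis, on adjustment: "The preselected demographic and background characteristics (covariates) will be added to evaluate whether the intervention effects on primary outcomes remain significant". The baseline value of the outcome is not named among these covariates.
- Sample Size: the 80% power is for a standardised effect of 0.41 "when comparing the mean change scores of the primary outcome between intervention and control conditions".

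Data Collection lists baseline and the 3-, 6-, 9- and 12-month visits. The natural reading is that baseline is one level of the visit factor and that the contrast is the condition-by-visit term.

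**The concern.** With baseline among the outcome visits and a condition main effect in the model, the baseline mean is estimated separately in each arm. With an identity link, the interaction contrast is follow-up minus baseline in one arm, less the same in the other. That amounts to adjusting for baseline with a slope fixed at 1. If the article instead means that change scores are the response at follow-up visits only, the slope is still 1.

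Because allocation follows baseline, the true baseline difference between arms is zero. Estimating it and subtracting it in full adds noise. It also over-corrects: when one arm starts higher by chance, its scores tend to fall back relative to the other arm, and the raw change counts that fall as effect. Pairing does not remove this, since communes are paired on the number of people who use drugs and not on the score. At stake is precision that could be had from data already collected, and some protection against an unlucky allocation of 60 communes.

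**Working it through.** **Inputs from the article.** 30 communes per arm; 12 participants per commune; attrition up to 8%, so m = 12 × 0.92 = 11.04 analysable; baseline plus four follow-ups; effect 0.41, power 80%, significance level 5% (two-sided assumed).

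**Not given, so assumed.** Individual baseline/follow-up correlation r = 0.3, 0.5, 0.7; ICC of the score from 0 to 0.25; identity link; an approximately continuous score; the same correlation between any two visits.

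**The article's own figure.** Without clustering, n per arm = 2 × (1.960 + 0.8416)² / 0.41² = 2 × 7.849 / 0.1681 = 93.4, that is 94. The plan has 360 × 0.92 = 331.2 analysable per arm. The ratio 331.2 / 93.4 = 3.55 would be the design effect, giving ICC = (3.55 − 1) / (11.04 − 1) ≈ 0.25. Using 12 per commune and then dividing by 0.92 gives about 0.23. So 720 can be reached only with an ICC that is not stated. It is neither confirmed nor refuted, and the article does not say on which scale clustering was allowed for.

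**Correlation of commune means.** Allocation is by commune, so what matters is the baseline/follow-up correlation R of commune means. With the stable commune and participant intercepts that the article names:

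R = [ICC + (r − ICC)/m] / [ICC + (1 − ICC)/m]

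Example, ICC 0.05 and r = 0.3: (0.05 + 0.25/11.04) / (0.05 + 0.95/11.04) = 0.0726 / 0.1361 = 0.534. At ICC 0.25 and r = 0.3: 0.2545 / 0.3179 = 0.801.

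**Variance saved by a common baseline mean.**

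- 12-month contrast: the raw change has variance proportional to 2(1 − R), the constrained contrast 1 − R². Saving = (1 − R)/2.
- Average of four follow-ups: 1.25(1 − R) against (1 − R)(1 + 4R)/4. Saving = 0.8(1 − R).

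Example, ICC 0.05 and r = 0.3: (1 − 0.534)/2 = 23% and 0.8 × 0.466 = 37%. Generalised least squares on commune means over five visits gives the same values:

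| Contrast | ICC | r = 0.3 | r = 0.5 | r = 0.7 |
|---|---|---|---|---|
| 12 months | 0 | 35% | 25% | 15% |
| 12 months | 0.05 | 23% | 17% | 10% |
| 12 months | 0.10 | 17.5% | 12.5% | 7.5% |
| 12 months | 0.25 | 10% | 7% | 4% |
| Average of four | 0 | 56% | 40% | 24% |
| Average of four | 0.05 | 37% | 27% | 16% |
| Average of four | 0.25 | 16% | 11% | 7% |

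If half the commune variance changes from visit to visit, the 12-month savings become 32%, 25% and 18% at ICC 0.05, and 28%, 25% and 22% at ICC 0.25.

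**Power.** Suppose the planned contrast has exactly 80% power at 0.41. Power after the change is Φ(2.80/√(1 − saving) − 1.96). For the 12-month contrast at ICC 0.05, savings of 23.3%, 16.6% and 10.0% give about 89%, 87% and 84%. At ICC 0.25, savings of 10.0%, 7.1% and 4.3% give about 84%, 83% and 82%.

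**Conditional bias.** Given an observed baseline difference d between arms, the raw-change contrast is shifted by −(1 − R)d. Ignoring the pairing, one standard deviation of d at ICC 0.05 is √(2 × 0.1361/30) = 0.095 score SD. At r = 0.3 the shift is then 0.466 × 0.095 ≈ 0.044 score SD. Over all allocations it averages to zero.

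**The case against.** The strongest defence is that nothing here is wrong. A mixed model with a condition-by-visit contrast is a standard, valid analysis of a randomised trial and is unbiased over randomisations. Planning and analysis agree: both use the change from baseline, so the stated power belongs to this very contrast. All of that stands.

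Three stronger readings are tempting and are not supported.

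- A reader might infer that the trial is biased or underpowered. It is not shown to be. The regression-to-the-mean point holds only conditionally on an observed chance imbalance.
- A reader might take a flat saving of 15% to 35%, with power of about 86% to 94%, from the familiar (1 − r)/2. That formula assumes one follow-up and no clustering, or equal correlation at participant and commune level. The article names commune and participant random effects and no commune-by-visit term. A stable commune effect cancels in a change score, so commune means correlate more strongly than individual scores and the 12-month saving is smaller.
- A reader might treat ICC 0.25 as the planners' value. It is only a back-calculation that assumes a simple design effect.

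Two limits also stand. The link function is left open, and the formulas need an approximately continuous outcome with an identity link; the standardised mean-change effect in Sample Size supports this for the primary score. The article is also a condensed account, and a full analysis plan could constrain the baseline. The model it does state has no such constraint, so this is a point about a stated choice and not about missing detail.

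**Conclusion.** The point holds as lost efficiency plus conditional sensitivity to chance baseline imbalance. For a linear score, the common-baseline or baseline-adjusted analysis is never less precise in large samples, and the saving was positive in every scenario examined.

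Under the article's own random-effects structure and r of 0.3 to 0.7, the 12-month saving is modest: about 23% to 10% of the variance at ICC 0.05, and 10% to 4% at ICC 0.25. It is larger for an averaged contrast, with little clustering, or with commune-by-visit variation. Since the article gives none of r, the ICC or the contrast, no single figure should be quoted. The change is worth making because it costs almost nothing, not because the planned analysis fails.

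**What to change.** For the primary score and other approximately continuous outcomes (domain scores and secondary measures where this applies), take one of two equivalent routes:

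1. Keep baseline as an outcome visit and constrain the arms to a common baseline mean: drop the condition main effect, and keep visit and condition-by-post-baseline-visit.
2. Model only the 3- to 12-month scores, with the participant's baseline score and its commune mean as covariates.

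Name the route before any data by arm are seen, so that it cannot depend on how the baseline turns out. Leave the sample size alone: "We propose enrolling 720 PWUD (360 per condition) to ensure we have 80% power at 5% significance level" at an effect of 0.41 can stay as the conservative planning statement. The cost is a change of model wording; no extra visits, data or participants are needed.

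### Read as random intercepts, the named random effects drop out of the primary comparison of change, so commune-level clustering of change is not allowed for and type I error can exceed 5%

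*Protocol article*

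**What the plan says.** All quotations are from the protocol article.

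- **Design** (Sample Size): "The study will randomize 60 CHCs (clusters) to intervention and control conditions with a 1:1 ratio". Study Design gives 12 families per commune health center, hence 720 people who use drugs, 360 per arm.
- **Target** (Data Analysis): the models are to "compare the changes in the primary outcome from baseline between intervention and control groups".
- **Fixed part** (Data Analysis): "The main effects included in each model are intervention condition, visit, and a condition-by-visit interaction term".
- **Random part** (Data Analysis): "Each regression model will include commune- and participant-level random effects to account for dependence within communes and repeated observations within participants".
- **Estimate** (Data Analysis): "Intervention effects on the primary outcomes will be estimated using model contrasts". No visit or average over visits is singled out.
- **Sizing** (Sample Size): the calculation concerns the difference in mean change, with standardized effect 0.41, 80% power, 5% significance and attrition up to 8%. It adds: "The proposed sample size accounts for the commune-level clustering". No ICC is given.

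The article names no commune-by-visit effect, commune slope, robust variance or between-commune degrees of freedom. It also does not say that the random effects are intercepts only.

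**The concern.** A commune intercept describes how communes differ in level. The hypothesis concerns how they differ in change. An intercept takes the same value at baseline and at 12 months, so subtracting one from the other removes it, and the participant intercept goes the same way. What remains to judge the contrast is person-level residual error spread over 360 people per arm. The 30 randomised communes per arm do not enter.

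That is harmless only if people in the same commune do not change together. Here they plausibly do. According to Intervention Implementation, the health workers of a commune deliver services as a team, and the primary score measures service engagement, which such a team affects directly. Any shared improvement or decline in a commune would be counted as many independent changes. Standard errors would then be too small, and ordinary commune-to-commune drift could pass for an intervention effect.

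**Working it through.** **1. The plan's own figure.** Inputs from Sample Size: effect 0.41, power 80%, alpha 5% (two-sided assumed), attrition 8%. Without clustering, n per arm = 2 × ((1.96 + 0.84)/0.41)² = 93.4, so 94, or 94/0.92 = 103 with attrition (206 in total). The stated 720 therefore contains a large allowance. It cannot be reproduced, because no ICC is given.

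Solving backwards, 360 × 0.92 = 331.2 evaluable per arm and 12 × 0.92 = 11.04 per commune. The implied design effect is 331.2/93.4 = 3.55, and the implied ICC is (3.55 − 1)/(11.04 − 1) = 0.25. This assumes that 0.41 is in standard deviations of change. Other assumptions give 0.24 (t test with 58 df), 0.26 (attrition ignored), 0.15 (alpha divided by 4) and 0.35 (one-sided).

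**2. Variance of the contrast.** Let within-person variance be σ² = σ²_ct + σ²_e, where σ²_ct is the commune-by-visit part. Put ρ = σ²_ct/σ², which is also the ICC of change. With n = 360 people per arm, in communes of m = 12:

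- variance used by the intercepts-only model for the 12-month contrast: about 4σ²/n
- true variance: (4σ²/n) × [1 + (m − 1)ρ]

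The closed-form standard error was compared with restricted maximum likelihood fits of the model with commune and participant intercepts. The ratio was 1.000 in 60 fits.

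**3. Type I error.** The formula is 2 × [1 − Φ(1.96/√(1 + 11ρ))]. At ρ = 0.05, for example, the design effect is 1.55 and 1.96/1.245 = 1.574, which gives 11.5%. The simulations used 4,000 null trials per ρ, with 30 communes per arm, 12 people each, 5 visits and no attrition.

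| ρ (assumed) | Formula, 12 months | Simulated, 12 months | Simulated, average of follow-ups | Simulated, joint 4-df test | Commune mean changes, t with 58 df |
|---|---|---|---|---|---|
| 0 | 5.0% | 4.9% | 4.7% | 5.3% | 4.9% |
| 0.01 | 6.3% | 6.2% | 5.8% | 7.2% | 5.0% |
| 0.02 | 7.6% | 7.5% | 7.4% | 10.2% | 4.5% |
| 0.05 | 11.5% | 11.7% | 10.5% | 18.7% | 4.7% |
| 0.10 | 17.6% | 18.1% | 17.8% | 34.4% | 4.6% |

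A second simulation with 11 people per commune gave 5.1%, 6.3%, 6.8%, 11.2% and 16.1% for the 12-month contrast at the same values of ρ. The 58 degrees of freedom are 60 communes less two arm means and ignore the pairing of communes.

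**The case against.** The cancellation holds for one model: the score at all five visits as response, with random intercepts only. The article does not say that this is the model.

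- **Form of the random effects.** The text speaks of random effects at two levels. Slopes or a commune-by-visit term are not listed, but not ruled out, and a condensed article often leaves such detail to the full protocol or analysis plan.
- **Response variable.** If the response were the change score at follow-up visits, a commune intercept would itself be a commune deviation in change. It would not cancel, and it would absorb drift that persists over follow-up.
- **Consistency with the sizing.** Both sections state an intention to handle commune clustering, so a reader who infers a flat contradiction between them goes too far.
- **Size.** No commune-by-visit variance is given. At ICC 0 there is no inflation, and at 0.01 about one percentage point.

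All four points stand as limits on the claim, and none removes it. The article lists the fixed and random parts of the model and offers the two random effects as what accounts for dependence within communes. In their usual meaning they do not do this for change. The raw-score reading is also the more natural one, since link functions and a participant effect for repeated observations suit scores better than differences. The gap is therefore in a choice that the article makes, and goes beyond a missing detail.

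**Conclusion.** The point holds in conditional form. As ordinarily read, the named model leaves commune-correlated change out of the standard error of the primary contrast, while the Sample Size section treats that correlation as something to be allowed for. The test should match the sizing. At a nominal 5%, the true level would be about 6% at an ICC of change of 0.01, 7 to 7.5% at 0.02, 11 to 12% at 0.05 and 16 to 18% at 0.10. These figures rest on a continuous score, independent commune-by-visit effects and the 12-month contrast. The ICC range is an assumption.

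Two stronger readings are tempting and are not supported. One is that false positives are certainly inflated: that needs both the intercepts-only form and a positive commune-by-visit variance, and the article establishes neither. The other is that the plan's own figures imply a type I error of about 30% (simulated 29% at ICC 0.24 and 32% at 0.25). That ICC is solved back from the sample size and assumes that 0.41 is in standard deviations of change. If it were in standard deviations of the score, the design effect would be 3.55/[2(1 − r)], where r is the baseline-to-follow-up correlation. The implied ICC would then be about 0.08 at r = 0, 0.14 at r = 0.25 and 0.25 at r = 0.5. In any case, a planning allowance is not evidence of actual drift.

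This is a cheap improvement to make before outcome data are analysed.

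**What to change.** In Data Analysis, state the response variable and the form of the random effects. Add a commune-by-visit random effect, or commune random slopes, and test the primary contrast with between-commune degrees of freedom. Alternatively, make an analysis of commune-level mean changes the primary or confirming test. In the simulations it kept to 4.5 to 5.0% over the range tabulated. The within-person covariance and the particular degrees-of-freedom method can be left to the analysis plan.

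The cost is wording and somewhat wider intervals. The standard error grows by √(1 + 11ρ), a factor of 1.05 at ICC 0.01, 1.24 at 0.05 and 1.45 at 0.10, and the critical value moves from 1.96 to 2.00. No participants need be added. With 331 evaluable per arm and 0.41 in standard deviations of change, the power of a 58-df test is 99% at ICC 0.05, 96% at 0.10 and still 80% at 0.24.
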